### Data collection and data management

Data will consist of information obtained by the Collabri Flex team (from baseline throughout the study period), self-reported questionnaire data and register data.

The baseline diagnostic eligibility interview is supervised by and delegated by the psychiatrist. The diagnostic assessment is based on the Mini International Neuropsychiatric Interview (MINI) [40], in which all care managers have received extensive training. The psychiatrist is always consulted to discuss the assessment and clinical impression. If there is disagreement between the result of the diagnostic assessment and the GP’s referral diagnosis, the psychiatrist contacts the GP to agree on the primary diagnosis and potential secondary diagnoses. In connection with the diagnostic assessment, the care manager obtains additional baseline information using the Standardized Assessment of Personality Abbreviated Scale (SAPAS) [41] and, if relevant, the Attention-Deficit/Hyperactivity Disorder Symptom Checklist for Adults (Adult ADHD Self-report Scale (ASRS)) [42]. Self-reported questionnaires will be completed electronically before the diagnostic assessment and 6 months after randomization.

Diagnostic assessment data, intervention-specific data and self-reported questionnaire data are collected through and stored in the electronic system REDCap [43], which is the data management system required by the Capital Region of Denmark. Other data, such as data extractions for quality assurance, are stored in entry-restricted files on secured and logged servers. Blinding will be maintained.

### Outcomes

In the depression trial, the primary outcome is symptoms measured by the Beck Depression Inventory (BDI-II) [44]. The BDI-II is a self-reported 21-item general depression questionnaire, measuring depression symptoms during the past 14 days. Symptoms are rated on a 4-point Likert scale ranging from 0 to 3. In a review of the psychometric properties of the BDI-II, the authors reported a high internal consistency (Cronbach’s α ranging from 0.83 to 0.96) and a test–retest reliability (Pearson’s *r*) ranging from 0.73 to 0.96 [45]. In primary care patients, the questionnaire has shown reliable and internally consistent scores [46].

In the anxiety trial, the primary outcome is symptoms measured by the Beck Anxiety Inventory (BAI) [47]. The BAI is a self-reported 21-item general anxiety questionnaire, measuring anxiety symptoms during the past week. Symptoms are rated on a 4-point Likert scale ranging from 0 (never) to 3 (almost all the time). The questionnaire has demonstrated high internal consistency (Cronbach’s α = 0.92) and a 1-week test–retest reliability of 0.75 in a group of outpatients mainly with anxiety or depression [48]. In a primary care setting, the BAI has been shown to reflect the severity of anxiety in patients with different anxiety disorders [49].

In both trials, the self-reported secondary outcomes are general psychological problems and symptoms measured by the Symptom Checklist (SCL-90-R) [50], functional impairment measured by the Sheehan Disability Scale (SDS) [51–53] and well-being measured by the World Health Organization-Five Well-Being Index (WHO-5) [54, 55]. In the anxiety trial, the BDI-II is an additional secondary outcome, and the BAI is an additional secondary outcome in the depression trial.

The SCL-90-R is a questionnaire designed to assess a broad range of general psychological problems and symptoms. This multi-dimensional questionnaire consists of 90 items rated on a 5-point Likert scale ranging from 0 (not at all) to 4 (extremely). The items are divided into nine subscales (depression, anxiety, phobic anxiety, obsession/compulsion, hostility, somatization, interpersonal sensitivity, paranoid ideation and psychoticism) from which the joint measure, the Global Severity Index (GSI), can be calculated as the average score of the 90 items.

The SDS includes three items and measures functional disability in relation to work, social and family life. For each item there are 11 potential responses reflecting the degree of impairment, ranging from 0 (not at all) to 10 (extremely). A total score ranging from 0 (not impaired) to 30 (highly impaired) can be calculated.

The WHO-5 includes five items measuring the experience of positive psychological well-being. Each item is rated from 0 (not present) to 5 (constantly present) on a 6-point Likert scale.

Explorative outcomes in both trials are self-reported health-related quality of life measured by the EuroQol Five Dimensions Questionnaire (EQ-5D-3 L) [56]; self-efficacy measured by the *Personal Control* subscale from the Illness Perception Questionnaire Revised (IPQ-R) [57] and two subscales (*Obtain Help from Community, Family, Friends Scale* and *Control/Manage Depression Scale*) from the Chronic Disease Self-Efficacy Scales [58]; experience of support in personal recovery measured by INSPIRE [59]; general satisfaction with treatment measured by the Client Satisfaction Questionnaire (CSQ-8) [60, 61]; sick leave; employment; and outpatient mental-health services obtained from registers (see Table 2 and Fig. 3 for an overview of primary, secondary and explorative outcomes). The EQ-5D-3 L measures health-related quality of life in five domains: mobility, self-care, usual activities, pain/discomfort and anxiety/depression. The assessment also contains a visual analog scale ranging from 0 (worst imaginable health status) to 100 (best imaginable health status). The IPQ-R consists of 12 subscales and the *Personal Control* subscale is a six-item scale reflecting a person’s beliefs about their ability to affect own symptoms. The items are rated on a 5-point Likert scale ranging from 1 (disagree very much) to 5 (agree very much). The *Obtain Help from Community, Family, Friends* subscale from the Chronic Disease Self-Efficacy Scales consists of four items about how confident the person feels in getting emotional support and help with daily tasks from the community, family and friends. The *Control/Manage Depression* subscale from the Chronic Disease Self-Efficacy Scales consists of six items regarding how confident the person feels about doing something to feel better when feeling sad, discouraged or lonely. Each item on these two subscales is rated on a 10-point Likert scale ranging from 1 (not at all confident) to 10 (very confident). The INSPIRE questionnaire measures the patients’ feelings of being supported in their recovery by their primary health-care provider(s). The questionnaire has two sections: one assessing support from the health-care provider (20 items); and one assessing the relationship with the health-care provider (seven items). General satisfaction with treatment is assessed through the CSQ-8 questionnaire, which consists of eight items rated on a scale ranging from 1 to 4. Information about sick leave and employment is obtained from the Danish Register for Evaluation of Marginalization (DREAM) database [62]. Information about outpatient mental-health contacts is collected through the National Patient Register, which contains information about all patient contacts in the secondary health-care system [63].

**Table 2 Tab2:** Outcomes, data source and time for data collection

Data source	Outcome		Baseline	6-month follow-up
Questionnaire	Anxiety symptoms measured by the Beck Anxiety Inventory (BAI)	Primary outcome in the anxiety trial, secondary outcome in the depression trial	x	x
Questionnaire	Depression symptoms measured by the Beck Depression Inventory (BDI-II)	Primary outcome in the depression trial, secondary outcome in the anxiety trial	x	x
Questionnaire	Functional impairment measured by the Sheehan Disability Scale (SDS)	Secondary outcome	x	x
Questionnaire	General psychological problems and symptoms measured by the Symptom Checklist (SCL-90-R)	Secondary outcome	x	x
Questionnaire	Psychological general well-being measured by the World Health Organization-Five Well-being Index (WHO-5)	Secondary outcome	x	x
Questionnaire	Self-efficacy related to symptoms measured by the *Personal Control* subscale from the Illness Perception Questionnaire Revised (IPQ-R)	Explorative outcome	x	x
Questionnaire	Self-efficacy related to management of disease measured by the *Control/Manage Depression* subscale from the Chronic Disease Self-Efficacy Scales	Explorative outcome	x	x
Questionnaire	Self-efficacy related to support from others measured by the *Obtain Help from Community, Family, Friends* subscale from the Chronic Disease Self-Efficacy Scales	Explorative outcome	x	x
Questionnaire	Health-related quality of life measured by the EuroQol five-dimension three-level version of health-related quality of life (EQ-5D-3L)	Explorative outcome	x	x
Questionnaire	Satisfaction with treatment measured by the Client Satisfaction Questionnaire (CSQ-8)	Explorative outcome		x
Questionnaire	Feeling of being supported in personal recovery by the primary health-care provider measured by the INSPIRE measure	Explorative outcome		x
DREAM database	Sick-leave benefit (yes/no) at follow-up and weeks on sick-leave benefit from baseline to follow-up	Explorative outcomes	x	x
DREAM database	Employment (yes/no) at follow-up and weeks in employment from baseline to follow-up	Explorative outcomes	x	x
National Patient Register	Mental-health outpatient contacts from baseline to follow-up	Explorative outcome	x	x

*DREAM* Danish Register for Evaluation of Marginalization

### Other data collection

Descriptive information about sex, age, housing and education is collected through Statistics Denmark, which is the central authority on Danish statistics [64]. Information about workforce participation is collected through the DREAM database [62]. Information about former treatment for anxiety or depression is collected through the National Patient Register [63] and information about screening for personality disorder is based on the Standardized Assessment of Personality (SAPAS) [41].

Collaborative care-specific data, such as use of treatment modalities, number of step-ups and sessions, will be registered by the Collabri Flex team throughout the intervention period. Information about consultations between the patient and GP will be registered in both the collaborative care and consultation liaison group at 1, 3 and 6 months and patient-specific communication between professionals will be registered continuously.

### Safety measures

Safety measures are self-reported anxiety and depression symptoms measured by the BAI [47] and BDI-II [44]; deaths from suicide and other causes collected through the Danish Register of Causes of Death [65]; and somatic inpatient and outpatient services and psychiatric inpatient services obtained from the National Patient Register [63].

### Sample size and power calculations

#### The Collabri Flex Trial for Depression

Clinically relevant treatment response at group level is defined as a 4-point difference in depression symptoms measured by the BDI-II [66, 67]. At the time of sample size calculation, we found no relevant Danish studies that could contribute to the estimation of the within-group standard deviation (SD) for the BDI-II in this population. Therefore, the SD for the BDI-II is set to 11, based on international surveys [66–68]. A sample size calculation based on these figures shows that 240 participants should be included to be able to reject the null hypothesis that the collaborative care group and the consultation liaison group have improved similarly in terms of symptoms with a power of 0.8 and a significance level of 0.05.

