#### The Collabri Flex Trial for Anxiety

Clinically relevant treatment response is defined as a 4-point difference in anxiety symptoms measured with the BAI. The estimation is based on studies using the BDI [66, 67], because, to our knowledge, there are no comparable Danish studies using the BAI. Additionally, we could not find any Danish studies that could contribute to the estimation of the SD for the BAI in this population. Therefore, the SD is set to 12 based on international surveys [68–70]. Based on these figures, the sample size calculation shows that 284 individuals should be included in the anxiety trial to be able to reject the null hypothesis that the collaborative care group and the consultation liaison group have improved similarly in terms of anxiety symptoms with a power of 0.8 and a significance level of 0.05.

Power calculations for the secondary outcomes showed that 120 participants in each group in the depression trial and 142 participants in each group in the anxiety trial will be sufficient to detect relevant significant differences in the secondary outcomes with a power above 80% (see Tables 3 and 4). The power calculations were performed subsequent to the sample size calculations. Some of the figures are based on Collabri data that were not available at the time of sample size calculations.

**Table 3 Tab3:** Power calculations for secondary outcomes in the depression trial

	δ value for clinically relevant difference	α value for type I error	σ value for the within-group SD	Calculated power	Reference
BAI	4	0.05 (5%)	10	0.870 (87.0%)	[66, 67] SD is based on data from the Collabri depression trial (not published)
SDS	4	0.05 (5%)	9	0.930 (93.0%)	[51, 52, 71]
SCL-90-R	23	0.05 (5%)	50	0.944 (94.4%)	[72]
WHO-5	10	0.05 (5%)	18	0.990 (99.0%)	[55, 73] SD is based on data from the Collabri depression trial (not published)

*BAI* Beck Anxiety Inventory, *SCL-90-R* Symptom Checklist 90-Revised, *SD* standard deviation, *SDS* Sheehan Disability Scale, *WHO-5* World Health Organization-Five Well-being Index

**Table 4 Tab4:** Power calculation for secondary outcomes in the anxiety trial

	δ value for clinically relevant difference	α value for type I error	σ value for the within-group SD	Calculated power	Reference
BDI-II	4	0.05 (5%)	11	0.863 (86.3%)	[66–69]
SDS	4	0.05 (5%)	10	0.920 (92.0%)	[51, 52, 71]
SCL-90-R	23	0.05 (5%)	50	0.972 (97.2%)	[72]

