### Statistical analyses

The null hypothesis tested in both trials is that there is no difference in depression and anxiety symptoms, respectively, between the two groups (collaborative care and consultation liaison) at 6 months’ follow-up. For continuous outcomes, including the primary outcomes, analysis of variance (ANCOVA) will be used to examine differences between group means. For exploratory binary outcomes, logistic regression analysis will be used to detect differences between groups. All analyses will be adjusted for stratification variables. The trials will be conducted according to the statistical principle “intention-to-treat”, which means that analyses will be based on all included participants. If necessary, multiple imputations will be used to address the issue of missing data.

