## Discussion

The design of the trials has several strengths. The collaborative care model has been developed based on previous experiences and with special emphasis on meeting the needs of GPs. We hope this will increase the success of any subsequent implementation; fidelity reviews will be conducted to ensure faithfulness to the intervention; we recognize the risk of contamination of the control group when testing a system-level intervention, and therefore we compare the collaborative care group with a form of consultation liaison that equals the contaminating elements; the randomization is externally computer generated, which reduces the risk of selection bias; compared with the Collabri trials, the questionnaire battery has been shortened to enhance the follow-up rate; and the psychiatrist in the Collabri Flex team and many of the care managers and GPs also participated in the previous Collabri trials, and, accordingly, they have already worked within the framework of the similar Collabri model and have experienced being part of an RCT.

The design of the trials also has some limitations. Most outcomes, including the primary outcomes, are self-reported, which could lead to information bias and, possibly, overestimation of effects [74]; participants, the Collabri Flex team and GPs are not blinded to the allocation, which could lead to performance bias; because we compare two active intervention groups, it might be more difficult to detect a difference between groups than if we had compared collaborative care with treatment as usual; thus, accordingly, from these trials we will not be able to conclude whether collaborative care is more effective than treatment as usual. However, the results will supplement those of the cluster-randomized Collabri trials and together they will provide pivotal information about the effects of collaborative care in Denmark.

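### The primary sample sizes of 240 and 284 give 80% power only with complete 6-month data, but they are stated as numbers to include with no allowance for loss

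*Protocol article*

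**What the plan says.** In the protocol article's section on sample size and power calculations, the clinically relevant response in the depression trial is "defined as a 4-point difference in depression symptoms measured by the BDI-II", and "the SD for the BDI-II is set to 11, based on international surveys". From these the article concludes that "240 participants should be included to be able to reject the null hypothesis"; the calculation is made "with a power of 0.8 and a significance level of 0.05". The anxiety trial uses a 4-point difference on the BAI and an SD of 12, and concludes that "284 individuals should be included in the anxiety trial to be able to reject the null hypothesis", again with power 0.8 at level 0.05.

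For the secondary outcomes the statement is: "120 participants in each group in the depression trial and 142 participants in each group in the anxiety trial will be sufficient to detect". The power claimed for those differences is over 80%. Tables 3 and 4 list values from 86.3% to 99.0%.

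On incomplete data, the Statistical analyses section says: "If necessary, multiple imputations will be used to address the issue of missing data". The Discussion counts among the strengths, in comparison with the earlier Collabri trials, that "the questionnaire battery has been shortened to enhance the follow-up rate". Both primary outcomes are self-reported, with one questionnaire at baseline and one at 6 months (Tables 1 and 2). No expected loss or response rate is given.

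**The concern.** A sample-size calculation yields the number of patients who must supply an outcome. The number to include is larger unless every patient supplies one. Here the two numbers are the same, yet the article makes provision for missing outcomes. The stated power for the primary outcome therefore rests on a condition that the article does not state.

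The comparator is active, and the Discussion accepts that a difference may be harder to detect for that reason. If the trials are reported as having 80% power when the completers supply less, a null result is likely to be over-read as evidence against a 4-point difference.

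**Working it through.** **Inputs.** Difference 4 in both trials; SD 11 (BDI-II) and 12 (BAI); power 0.80; significance level 0.05; equal arms of 120 and 142. All are in the sample-size section. Sidedness is not stated and is taken as two-sided: one-sided testing would give totals of 188 and 224, which do not match.

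**Step 1: reproduce the stated numbers.** By the normal approximation, n per arm = 2 × [SD × (1.960 + 0.8416) / difference]².

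- Depression: 2 × (11 × 2.8016 / 4)² = 2 × 7.704² = 118.7, so 119 per arm. The two-sample t-test needs 119.7, so 120 per arm and 240 in total.
- Anxiety: 2 × (12 × 2.8016 / 4)² = 2 × 8.405² = 141.3, so 142 per arm and 284 in total. The t-test needs 142.2 per arm.

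Power by t-test at 120 and 142 per arm is 0.801 and 0.799. Both stated totals are reproduced with zero loss and practically no slack.

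**Step 2: power with loss.** The article gives no rate, so the loss d is an assumed range. Power = Φ(difference / (SD × √(2/m)) − 1.960), with m = n(1 − d) completers per arm. Example, depression with d = 20%: m = 96, SD × √(2/m) = 1.588, 4 / 1.588 = 2.519, and Φ(0.559) = 0.712.

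| Assumed loss | Depression, m per arm | Power, normal (t-test) | Anxiety, m per arm | Power, normal (t-test) |
|---|---|---|---|---|
| 0% | 120 | 0.804 (0.80) | 142 | 0.802 (0.80) |
| 5% | 114 | 0.784 (0.78) | 134.9 | 0.782 (0.78) |
| 10% | 108 | 0.762 (0.76) | 127.8 | 0.760 (0.76) |
| 20% | 96 | 0.712 (0.71) | 113.6 | 0.710 (0.71) |
| 30% | 84 | 0.654 (0.65) | 99.4 | 0.652 (0.65) |

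**Step 3: what a baseline covariate could give back.** If the baseline score is in the ANCOVA and correlates r with the 6-month score, the residual SD is SD × √(1 − r²). The number needed is then multiplied by (1 − r²), so a loss of r² is offset: 9%, 16% or 25% for an assumed r of 0.3, 0.4 or 0.5. With r = 0.5 and 20% loss, the t-test power is 0.825 (depression) and 0.823 (anxiety).

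**Step 4: secondary outcomes.** All eight values in Tables 3 and 4 are reproduced at full n to within 0.3 percentage points. The loss at which each falls to 80% is 1 − n₈₀/n, where n₈₀ is the per-arm number from the Step 1 formula:

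| Outcome | Depression trial | Anxiety trial |
|---|---|---|
| BAI / BDI-II | 18% | 16% |
| SDS | 34% | 31% |
| SCL-90-R | 38% | 48% |
| WHO-5 | 58% | 25% |

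At 10% loss all eight stay above 80% (82.8% to 98.3%). At 20% only two fall just below, by t-test: BAI in the depression trial (0.787) and BDI-II in the anxiety trial (0.779).

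**The case against.** The best reply is that nothing is miscalculated. Both sample sizes and all eight tabulated powers are reproduced, and an article may leave an attrition assumption to the full protocol. The first part stands. The second does not help: the published inputs give 240 and 284 with nothing left over, so these totals contain no allowance.

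Five stronger readings may occur to a reader, and the document does not support them.

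- *The secondary-outcome claim also needs every patient to respond.* It does not. It has a margin of about 16% loss or more; only the exact tabulated percentages assume full follow-up.
- *The plan expects missing data, or the earlier trials had poor follow-up.* The imputation sentence is conditional. The Discussion reports no follow-up rate, and the Background attributes the earlier trials' difficulty to too few patients being included.
- *The trials will not have 80% power.* This is not shown. No loss rate is given, and the planned ANCOVA may gain precision. Its stratification variables include baseline depression severity in the depression trial. The baseline score is not named as a covariate and the sample-size section claims no such gain, so its size is unknown.
- *The SDs should be replaced by Collabri values.* The BAI SD of 10 in Table 3 comes from the Collabri depression trial, a different population from the anxiety trial. The article gives no Collabri SD for either primary outcome in its own population.
- *Imputation can recover nothing.* That is too absolute. Register data, and GP consultations recorded at 1, 3 and 6 months, could serve as auxiliary variables. With no intermediate questionnaire the recovery may be small, but the document does not settle it.

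**Conclusion.** The point holds for the two primary outcomes. The article uses the numbers of complete observations as the numbers to include, without saying that the stated power of 0.8 depends on complete 6-month data. On the article's own unadjusted calculation, the shortfall is about 2, 4, 9 and 15 percentage points at 5, 10, 20 and 30% loss. At 20% loss, the chance of missing a true 4-point difference rises from about 20% to about 29%.

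These sizes rest on loss rates assumed here, on equal loss in the two arms, on two-sided testing, and on no gain from covariates or imputation. The true power could be close to 0.8, or above it, if response is high or the baseline score is a useful covariate. The fault is an unstated condition on the headline power of both trials, and it is cheap to remove.

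**What to change.** Keep 240 and 284. In each primary sample-size paragraph:

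1. State that power 0.8 applies to 120 and 142 patients per arm with complete 6-month data, under an unadjusted two-sided comparison.
2. Give the expected 6-month response rate, its source, and the power at that rate. For illustration, 90% response gives about 0.76 and 80% about 0.71 in both trials.
3. Alternatively, if the baseline BDI-II or BAI score is a covariate in the ANCOVA, say so in the Statistical analyses section. Then give the power on the residual SD, with the correlation relied on and the expected loss. An assumed r of 0.5 with 20% loss gives about 0.82; the correlation needs its own justification for each scale.

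For Tables 3 and 4, a footnote that the values assume complete follow-up is enough.

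The cost is a few sentences and no extra patients. The stated power becomes less favourable unless a covariate gain is justified. Restoring 80% by inflating n/(1 − d) would instead take 300 and 356 patients at 20% loss; that is not proposed.
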